### Follow-up

Male and female participants will be followed up at the end of the 14-week intervention (approximately 4 months post male baseline interview) (Table 2, Fig. 1). All participants will be phoned, texted or emailed 1 to 2 weeks before the due date of each qualitative interview and the follow-up interview to arrange a suitable time to undertake it. Participants will also be reminded the day before the interview. Interviews will be by phone or videocall. If COVID-19 restrictions allow, face-to-face interviews may also take place. For men, face-to-face interviews will be in substance use treatment services, and for women, in substance use treatment services, women’s support services or services such as children’s centres or libraries.

**Table 2 Tab2:**
[figure not shown]
Schedule of enrolment, interventions and assessments

**Fig. 1 Fig1:**
[figure not shown]
Flow of participants through the study

### Intervention

The TIDieR (Template for Intervention Description and Replication) Checklist was used to describe the intervention (Table 3) [46]. The ADVANCE intervention focuses on developing participants’ strengths and developing healthy, non-abusing relationships. Working towards this requires them to set specific goals for reducing risk, such as changing substance use, and developing a prosocial lifestyle in terms of work, leisure, health and accommodation. Underpinning the goal-focused approach is the need to improve self-regulation of behaviours, achieved by identifying and changing cues, appraisals (thoughts), emotions, behaviours and consequences. Throughout the ADVANCE intervention, behaviour change skills are introduced and practised. The ADVANCE digital intervention includes the following:A one-to-one session with a facilitator to set goals, develop a personal safety plan and increase motivation and readiness to change (45 min).An online group session on the preparation for group and instructions on how to use the intervention (1 h 15 min).Six fortnightly online group sessions (1 h per group session).Online group session 1: Understanding abuseOnline group session 2: Handling challengesOnline group session 3: Difficulties in familiesOnline group session 4: Times of distressOnline group session 5: Relating wellOnline group session 6: Doing it differently12 weekly self-directed sessions on a bespoke website (approximately 30 min per session) recapping on and practising relevant skills from the online group sessionsWebsite session 1: Introduction to ADVANCEWebsite session 2: Managing myselfWebsite session 3: Being a manWebsite session 4: Impact on herWebsite session 5: Children and parentingWebsite session 6: RelatingWebsite session 7: Improving communicationWebsite session 8: Dealing with distressWebsite session 9: Planning to be betterWebsite session 10: Positive relationshipsWebsite session 11: New futures, peoples plans and positive activitiesWebsite session 12: Recap ‘what have we learned?’One-to-one support/coaching completed by a facilitator by phone/videocall after each website session (30 min per individual session).A group online group refresher session 1 month after the last online group (1 h) (Fig. 2).

**Table 3 Tab3:** The TIDieR (Template for Intervention Description and Replication) Checklist

Item number	Item	Where located	
		Primary paper (page or appendix number)	Other (details)
	**Brief name**		
**1.**	Provide the name or a phrase that describes the intervention.	Intervention (page 5)	
	**Why**		
**2.**	Describe any rationale, theory, or goal of the elements essential to the intervention.	Background (pages 12–14), Intervention (pages 12–14)	
	**What**		
**3.**	Materials: Describe any physical or informational materials used in the intervention, including those provided to participants or used in intervention delivery or in training of intervention providers. Provide information on where the materials can be accessed (e.g. online appendix, URL).	Intervention (pages 12–14)	
**4.**	Procedures: Describe each of the procedures, activities, and/or processes used in the intervention, including any enabling or support activities.	Intervention (pages 12–14)	_____________
	**Who provided**		
**5.**	For each category of intervention provider (e.g. psychologist, nursing assistant), describe their expertise, background and any specific training given.	Intervention (page 15)	_____________
	**How**		
**6.**	Describe the modes of delivery (e.g. face-to-face or by some other mechanism, such as internet or telephone) of the intervention and whether it was provided individually or in a group.	Intervention (pages 12–14)	_____________
	**Where**		
**7.**	Describe the type(s) of location(s) where the intervention occurred, including any necessary infrastructure or relevant features.	Intervention (page 7, 12–14)	
	**When and how much**		
**8.**	Describe the number of times the intervention was delivered and over what period of time including the number of sessions, their schedule, and their duration, intensity or dose.	Intervention (pages 12–14)	_____________
	**Tailoring**		
**9.**	If the intervention was planned to be personalised, titrated or adapted, then describe what, why, when, and how.	Intervention (pages 13, 14)	_____________
	**Modifications**		
**10.**	If the intervention was modified during the course of the study, describe the changes (what, why, when, and how).	N/A	_____________
	**How well**		
**11.**	Planned: If intervention adherence or fidelity was assessed, describe how and by whom, and if any strategies were used to maintain or improve fidelity, describe them.	Fidelity (page 16)	_____________
**12.**	Actual: If intervention adherence or fidelity was assessed, describe the extent to which the intervention was delivered as planned.	N/A	_____________

**Fig. 2 Fig2:**
[figure not shown]
ADVANCE digital intervention

In total, the intervention takes 21 h to complete over 18 weeks including the refresher session. Services can start the intervention once a minimum of six men have been recruited. Additional men can join the intervention up until week 3 (maximum 10 men per group).

The intervention will be delivered by two facilitators who are substance use treatment workers (where possible one male and one female). Two to three facilitators per substance use treatment service have been trained on screening, risk assessment, case management and intervention delivery. ISS workers have been trained on supporting women and case management.

Men will also receive their substance use treatment as usual (e.g. group work, individual sessions, mutual aid and opiate substitution treatment).

### Non-adherence

For additional men joining the intervention up to week 3 or for men who miss sessions, facilitators will update them on content they have missed during their scheduled weekly telephone coaching call and encourage them to complete the website sessions. Each website session also offers the opportunity to refresh what is covered in the previous group session. Every effort will be made to re-engage men in the intervention who miss sessions; however, if men do not engage in any group or website sessions during the first 3 weeks (or are discharged from the substance use service for non-attendance thereafter)—access to the website sessions will be revoked. If it is impossible to complete the groups as scheduled, any participant who has started the intervention will be helped to engage with the full content on an individual basis to avoid half completion of an intervention that would benefit them, with potential adverse impact.

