### Fidelity

Fortnightly online integrity support meetings led by EG (Clinical Forensic Psychologist) will be held for all facilitators and ISS workers to discuss delivery issues and address any expected problems with the next two sessions. These integrity support meetings will cover the core of the material to be delivered in the forthcoming sessions and review any issues that have arisen when delivering previous sessions to promote fidelity to the model and reduce likely non-adherence. Any deviation from delivery as planned will be noted and included as a factor in the evaluation of acceptability and feasibility.

All online group sessions will be recorded within Microsoft Teams with participants’ and facilitators’ consent. Researchers will check a random sample of 10% of the recording intervention fidelity, using a pre-defined checklist for each group session. In addition, recordings of the integrity management meetings will contribute to understanding fidelity.

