### Feasibility parameters

The feasibility of delivering the ADVANCE digital intervention to men in substance use treatment (including uptake of supporting female partner) will be assessed by the following:Number of men assessed using the Abusive Behavior Inventory (ABI) as eligible to participate/number of men screened (eligibility rates).Number of men B-SAFER as suitable to participate/number of eligible men (suitability rates).Number of men consenting to take part in the study/number of eligible men (recruitment rates men).Number of recruited men completing at least one session of the intervention/number of recruited men (uptake of intervention rates men).Number of current or ex-female partners recruited/number of men recruited (recruitment rates women).Number of women taking up the offer of support from the ISS/total number of female partners contacted by the ISS (uptake of support women).Number of recruited women viewing at least one session of the intervention and safety messages/number of recruited women (uptake of intervention rates women).

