### Acceptability parameters

The acceptability of the ADVANCE digital intervention to end users and substance use treatment staff will be assessed by the following:Number of sessions of the intervention attended/total number of sessions offered (intervention attendance/completion rates for male and website sessions viewed for female participants).Number of sessions with the ISS/total number of sessions offered (attendance with ISS worker rates for female participants).Men’s experience of using the intervention (men will be asked to rate their level of agreement with a series of statements regarding their experience of using the website sessions and select an emoji of how they are feeling at the end of these sessions).Acceptability of intervention to staff and male and female participants (qualitative interviews, see process evaluation).Number of men interviewed at the end of the intervention/ number of men recruited (follow-up rate men).Number of women interviewed at the end of the intervention/number of women recruited (follow-up rate women).Number of serious adverse events (e.g. hospitalisation and self-harm) during the study/number of participants (adverse events rate).

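### The pooled attendance ratio cannot show whether the online groups held, and it leaves open how individual replacements and cancelled groups are counted

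*Protocol article*

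**What the plan says.** Three sections of the protocol article bear on this.

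- **Non-adherence.** The trigger is "If it is impossible to complete the groups as scheduled", with no cause or threshold given. The consequence is that "any participant who has started the intervention will be helped to engage with the full content on an individual basis". A man who misses a session while his group continues is handled differently: "facilitators will update them on content they have missed during their scheduled weekly telephone coaching call".
- **Feasibility parameters and Acceptability parameters.** Attendance is "Number of sessions of the intervention attended/total number of sessions offered". The parenthesis after it separates men from women, but does not separate group, website, coaching or replacement sessions. Uptake by men is "Number of recruited men completing at least one session of the intervention/number of recruited men", which any type of session satisfies. Neither list counts groups that start and run to the end.
- **Fidelity.** "Any deviation from delivery as planned will be noted and included as a factor in the evaluation of acceptability and feasibility".

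**The concern.** The study is meant to supply parameters for a definitive randomised trial, and the Abstract names attendance among them. The intervention mixes formats that differ in how hard they are to sustain. A website session needs one man and a tablet, whereas a group session needs several men online together with facilitators. A single ratio over all formats is dominated by the individual components.

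If a group breaks down and its men continue individually, the ratio may barely move. Anyone planning the trial from that figure would learn little about whether the group component can be kept running, and no other listed parameter supplies the information.

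**Working it through.** **Inputs** (Intervention section, except where stated): one preparatory one-to-one session of 45 min; one preparatory online group of 1 h 15 min; six core groups of 1 h; 12 website sessions of about 30 min; 12 coaching sessions of 30 min, one after each website session; one refresher group of 1 h. Sixty men and seven services (Setting and participants).

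**1. The plan's own figure.** Hours = 0.75 + 1.25 + 6×1 + 12×0.5 + 12×0.5 + 1 = 21.0. This matches the stated 21 h, so the component list is complete.

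**2. Session count.** 1 + 1 + 6 + 12 + 12 + 1 = 33 per man. Group sessions are 1 + 6 + 1 = 8, or 24% of the total.

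**3. One man in a group that stops.** Assume the group stops after two of six core sessions, the refresher is also lost, and the man attends everything else. Group sessions lost = 4 + 1 = 5. Group sessions held = 1 + 2 = 3.

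| Counting rule | Rate |
|---|---|
| Replacements credited as attended | 33/33 = 100% |
| Cancelled groups removed from sessions offered, no credit | 28/28 = 100% |
| Planned denominator kept, no credit | 28/33 = 84.8% |
| Group sessions only, planned denominator, no credit | 3/8 = 37.5% |

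The first three rows all fit the stated ratio. The second produces 100% without crediting any replacement.

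**4. Sensitivity to the assumptions.**
- With one to four core groups held, the third row runs from 27/33 = 81.8% to 30/33 = 90.9%, and the group-only rate from 2/8 = 25.0% to 5/8 = 62.5%.
- If coaching calls are not counted as sessions, the total is 21 and the third row is 16/21 = 76.2% (71.4% to 85.7% over the same range).
- Full attendance is not needed for the effect. A man who attends 60% of what is held scores 0.6×28 = 16.8 sessions. His rate is 16.8/33 = 50.9% with no credit, 16.8/28 = 60.0% with cancelled groups dropped, and (16.8 + 5)/33 = 66.1% with all five replacements attended and credited. Group sessions alone give 0.6×3/8 = 22.5%.

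**5. Whole study.** Assume seven equal groups, so 60/7 = 8.57 men each, and 60×33 = 1,980 person-sessions.
- One group stopping as in step 3: 5×8.57 = 42.9 person-sessions, and 42.9/1,980 = 2.2 points between full credit and none. Counting only the four core sessions, 34.3/1,980 = 1.7 points.
- Two such groups: 4.3 points (3.5 on core sessions only).
- On group sessions alone, the denominator is 60×8 = 480, and one stopped group costs 42.9/480 = 8.9 points.

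The same event is therefore about four times as visible in a group-only rate (8.9/2.2).

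**The case against.** The strongest reply is that a stopped group would not be missed. The Fidelity section requires deviations to be noted and weighed in judging acceptability and feasibility, and a move to individual delivery is plainly a deviation. Online groups are recorded, integrity meetings take place fortnightly, and men and delivery staff are interviewed up to four times. This stands. A reader might infer that group failure would pass unseen and that the trial would be planned on a format that had not held; the documents do not support that. What they lack is a number, since a noted deviation has no denominator.

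A reader might also infer that the ratio counts replacement sessions as group attendance. It does not say so. Non-adherence speaks of helping men engage with the content, which need not create a countable session. Crediting is one permitted reading only.

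The size can also be overstated. Taken over 60×6 = 360 core group person-sessions, one rescued group would shift the rate by 34.3/360 = 9.5 points and two by 19. But the protocol defines no core-group rate. On the ratio it does define, the shifts are those in step 5. Nor do the documents say that facilitator time for individual delivery is left out of the costing.

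Finally, counting rules are often left to the full protocol or analysis plan, so their absence from an article is not a fault in itself. That is fair. However, the article does fix the ratio as pooled, and even the strictest count leaves it at 85% when most of the group programme has been lost.

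**Conclusion.** The point holds in a limited form. As stated, the attendance ratio cannot show whether the group component was sustained, and no listed parameter fills the gap. For a man whose group stops after two core sessions and loses the refresher, the pooled rate is 85% to 100% (down to 76% if coaching calls are excluded), against 37.5% for group sessions. Across the study, one such group moves the pooled figure by about 2 points. That small shift shows how insensitive the ratio is; it is not a large bias in the overall attendance rate.

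The figures rest on assumptions: the stopping point, loss of the refresher, otherwise full attendance, and seven equal groups. The documents give no probability that a group will stop. This is a cheap improvement to a feasibility parameter that the definitive trial needs. It does not invalidate the study.

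**What to change.** In Acceptability parameters, replace the pooled ratio for men with separate rates for group, website and coaching sessions. Define group attendance as sessions attended in the group divided by all group sessions scheduled, with cancelled groups kept in the denominator. Report individually delivered replacement sessions as their own rate.

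In Feasibility parameters, add the number of groups completing all six core sessions as scheduled divided by the number of groups started.

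The cost is one delivery-mode field on the attendance log and a few more rows in the results. The group attendance figure may look less favourable than the pooled one. The individual-delivery contingency in Non-adherence is left unchanged.

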### Risk management

The ADVANCE facilitators, substance use service treatment staff and the ISS worker will share information that relates to women’s safety and risk. Four case management meetings will be held between facilitators (and men’s substance use workers where possible) and ISS workers over the course of the intervention to manage risk to female partners and children. The DASH risk checklist (*Domestic Abuse*, Stalking and Harassment and Honour-Based Violence) [47] will be administered by the ISS worker to women who take up the offer of support to assess and manage risk. This will be conducted prior to the man beginning the intervention and the first case management meeting between the facilitators and the ISS workers. DASH is a simple tool for practitioners who work with adult victims of domestic abuse to help them identify those who are at high risk of harm and whose cases should be referred to a Multi-Agency Risk Assessment Conference (MARAC) meeting in order to manage their risk (score of 14 or above). Women engaging with ISS support will be updated about their current/ex-partner’s overall progress in the group and will be offered access to the same 12 ADVANCE intervention website sessions as their current or ex male partner for information, alongside support messages (e.g. If your current/ex-partner talks to you about using a ‘time out’, know that a safe time out is one that is agreed in advance between the two of you and is not used to continue abuse). They will not get access to their current or ex-partner’s user-generated information. They will also receive weekly telephone or video call support from their ISS worker throughout the duration of the intervention if required.

### Training

Facilitators, ISS workers and substance use treatment staff not delivering the ADVANCE intervention at the services involved in the study attended an online a 1-day training in the use of the B-SAFER tool, a structured professional judgement tool specifically designed to assess risk and vulnerabilities in situations of IPA (the clinical/risk lead is an accredited trainer) [45]. Two additional days of training were delivered on the ADVANCE intervention’s theory of change; the importance of enhancing and maintaining motivation throughout; the content of the individual, group and website sessions and coaching phone calls, including the opportunity to practice delivery, understanding the role of ISS, risk identification and reporting, case management and integrity support.

### Fidelity

Fortnightly online integrity support meetings led by EG (Clinical Forensic Psychologist) will be held for all facilitators and ISS workers to discuss delivery issues and address any expected problems with the next two sessions. These integrity support meetings will cover the core of the material to be delivered in the forthcoming sessions and review any issues that have arisen when delivering previous sessions to promote fidelity to the model and reduce likely non-adherence. Any deviation from delivery as planned will be noted and included as a factor in the evaluation of acceptability and feasibility.

All online group sessions will be recorded within Microsoft Teams with participants’ and facilitators’ consent. Researchers will check a random sample of 10% of the recording intervention fidelity, using a pre-defined checklist for each group session. In addition, recordings of the integrity management meetings will contribute to understanding fidelity.

### Process evaluation

Data will be collected at multiple time points to capture changes and impact over time for participants:Brief online feedback will be collected from all male participants completing the 12 website sessions using a short questionnaire. Questions on whether the session was completed and the length of time it took to complete, as well as how they were feeling at the end of the session (rated using emojis) will also be recordedResearchers will conduct brief individual qualitative interviews with male participants using phone or video calls up to four times (after website session 2 (managing myself), 6 (relating), 9 (planning to be better) and 12 (what have I learned? Refresher session) about their experience of using the digital intervention and any behaviour change. Participants will be encouraged to keep a diary of their experience after each session to facilitate their feedback over the course of the intervention.Google analytics will provide in-depth detail about the participants’ use of the website (number of times logged on, duration of time spent on website, completion of session).Researchers will conduct individual brief qualitative interviews or focus groups with intervention delivery staff up to four times (to correspond with the timeframe of the male interviews) during the intervention about their experience of delivering the intervention.Researchers will conduct brief qualitative interviews with all current or ex-female partners of male study participants who agree to take part in the research up to four times during the study about their experience of the intervention and any behaviour change by their current or ex-partner. These interviews will be by video or phone call. We will interview women at a time that suits them (informed by risk/safety issues, e.g. calling when partner/children are not around).

